**Fig. 2 Fig2:**
[figure not shown]
Cervico thoracic posture corrective orthotic (CTPCO). **a** Anterior part of CTPCO. **b** Posterior part of CTPCO. Other images demonstrating the ability to move in different directions: **a1** and **a2** anterior and posterior translation; **b1** and **b2** lateral translation left and right; **c1** and **c2** side bending right and left; **d1** and **d2** rotation left and right; **e1** extension; **e2** flexion

### Ambulatory mirror-image functional re-training via wearing of the 3D adjustable CTPCO

The patient will use the adjustable CTPCO and walk at an approximate speed of 2–3 miles per hour on a standard, motorized treadmill for 20 min, three times per week for 10 weeks. The brace will reverse (overcorrect) the abnormal posture according to the 3D posture analysis data. The facilitation of tissue remodelling using reverse posture training is called mirror-image exercise. An additional movie file shows this procedure in more detail (Additional file 3).

**Additional file 3:** Movie file showing ambulatory mirror image functional re-training through wearing a 3D adjustable CTPCO. (MP4 134029 kb)

The same physiotherapist will individually deliver the entire intervention programme. The physiotherapist has had 10 years of experience and received training in these manual techniques, thereby minimizing inter-therapist variation and increasing reliability.

Patients in both groups will be instructed to perform neck retraction/extension, scapular retraction and deep upper cervical flexor strengthening exercises at home, twice daily as their home routine. To accurately monitor the exercise times and the number of sets performed during the study, a pamphlet illustrating the exercises and a record sheet will be distributed to the patients.

The record sheets will be collected every week and analysed to calculate the mean exercise frequency per week and the mean exercise time per day. The record sheet analysis will reflect a high degree of compliance with the home exercise sessions.

Patients will be encouraged to practice the same home routine at least twice per week for up to three months after treatment, but the ambulatory mirror image functional re-training will be terminated after the initial 10 weeks or 30 visits of intervention. Patients will be contacted via the wechat application every 3 days to gather the record sheet and to inspire patients to continue the training.

### Data collection

The primary outcome in the present study will be measured as the feasibility outcomes of conducting an RCT. The secondary outcome will be measured by the visual analogue scale (VAS), neck disability index (NDI) and the 3D posture parameters measured by the GPS device. The primary and secondary outcomes will be measured at baseline, after 10 weeks and after 3 months of follow-up. The schedule of treatment and outcome assessments is presented in Table 1.

**Table 1 Tab1:** Schedule of treatments and outcome measures throughout the trial

	Baseline 0 weeks	Treatment period 10 weeks	Follow-up after 3 months
Measures			
Feasibility outcomes	√	√	
VAS	√	√	√
NDI	√	√	√
3D posture parameters	√	√	√
Treatments			
Ambulatory mirror image functional re-training through wearing 3D adjustable CTPCO		√	
Conventional treatment like moist hot pack, soft tissue mobilization, manual therapy, therapeutic exercise		√	

*VAS* visual analogue scale, *NDI* Neck Disability Index, *3D* three-dimensional, *CTPCO* cervico thoracic posture corrective orthotic

### Data collection

In this study, the primary outcome will be measured by feasibility outcomes of conducting an RCT. The secondary outcome will be measured by the Visual Analogue Scale (VAS), Neck Disability Index (NDI) and Three-dimensional posture parameters measured by GPS device. Both the primary and secondary outcomes will be measured at baseline, after 10 weeks and after 3 months of follow-up. The schedule of treatment and outcome assessments is presented in Table 1.

## Primary outcomes

The primary outcome of the study is the feasibility of conducting an RCT [34, 35]. The specific aspects of feasibility that will be monitored are listed below.

### Integrity of the study protocol

Integrity includes the appropriateness of inclusion criteria, training of the staff, clinic accessibility for patients, acceptability of the intervention to patients and physical therapists and the time required for patients and facilities to deliver the interventions. These data will be gathered from interviews with patients and practitioners/therapists on their willingness to participate in the study and their opinions on the research process.

### Recruitment and retention

Recruitment and retention data include procedures for patient enrolment (goal of at least 80% of eligible patients accepting to be enrolled), patient adherence to the intervention (goal of at least 80% of patients attending 75% of treatment sessions and completing 75% of the prescribed exercises) and patient losses to follow-up (goal of at least 80% of participants completing the follow-up) [36].

### Outcome measures

Questionnaires, physical impairment measures and methods to measure exercise intervention compliance (measured via exercise diaries) will be used to determine the completeness of outcome data collected.

### Randomization procedure

The appropriateness of the methods used to ensure the blinding of the outcome measurement assessor will be determined through post-study interviews that ask whether they were aware of the group allocation and whether they felt that the treatments were consistent.

### Primary outcome measure

Selection of the most appropriate primary outcome measure for a full-scale RCT will be determined using the patient-reported outcome measure with the largest between-group effect size, as long as the between-group difference is greater than the previously reported minimal important change for that outcome measure.

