### Interventions

Twenty-four patients will be randomized into two groups (study and control) using block randomization. Both groups will receive conventional treatment consisting of a moist hot pack, soft tissue mobilization, manual therapy and therapeutic exercises.

The study group will also undergo ambulatory mirror-image functional re-training via the wearing of a 3D adjustable CTPCO. Patients in both groups will attend 30 physical therapy treatment sessions over a 10-week period at three sessions per week and then follow-up after 3 months. Short-term follow-up evaluations will be performed after 10 weeks of interventions, and the long-term follow up will be performed 3 months after the end of the 10 weeks of treatment. The flow diagram for this trial is presented in Fig. 1.

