### Sample-size calculation

The sample size of a future, fully powered study will be estimated using sample-size calculations using the effect-size data from this pilot study. We will recruit 24 patients for two groups [37].

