## Secondary outcomes

### Visual analogue scale

Patients will be asked to indicate their perception of pain along a 10-cm line, with 0 (no pain) on one end and 10 (worst pain) on the other end. Patients will be asked to place a mark along the line to denote their level of pain [38]. The time frame will be pre-treatment, post-treatment 10 weeks and after 3 months of follow-up.

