### Statistical analysis

Results of primary outcome measures will be provided descriptively in tables and compared to the a priori established goals. To provide a recommendation for estimated sample size for a future full-scale RCT, between-group effect sizes and 95% confidence intervals (CIs) with Hedges correction will be calculated for changes in the secondary outcomes of VAS, NDI and 3D posture parameters. The mean ± standard deviation score for each of the subscales will be used in the calculation of the effect size. Estimated sample size will be determined using the between-subject effect size, with a minimum of 80% power (*α* = 0.05). The sample size will be increased to allow for an estimated 20% dropout rate. Statistical methods for the secondary outcome measures will be evaluated via comparisons of changes between groups. Complete case analyses will be performed to include outcomes from all patients who completed baseline and follow-up evaluations, as recommended in the Consolidated Standards of Reporting Trials (CONSORT) guidelines [39]. The between-group difference in change scores for each outcome measure from baseline to follow-up will be determined and reported as the means and 95% CI, using an analysis of covariance. Covariates of age and sex will be included in the analysis. All statistical analyses will be performed in SPSS version 23.0 software (IBM Corporation, Armonk, NY) with significance set at *P* < 0.05.

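### The full-scale primary outcome is chosen by the largest pilot effect above an important-change threshold, so the effect size that can reach the sample-size step is biased upward

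*Protocol article*

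**What the plan says.** Under Primary outcomes, the subsection Primary outcome measure selects the full-scale primary outcome as "the patient-reported outcome measure with the largest between-group effect size, as long as the between-group difference is greater than" a benchmark for each measure. The benchmark is described only as "the previously reported minimal important change for that outcome measure", with no value or source.

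The candidates come from Data collection: "The secondary outcome will be measured by the visual analogue scale (VAS), neck disability index (NDI) and the 3D posture parameters measured by the GPS". The posture parameters are not patient-reported, so only VAS and NDI compete. Both are measured at more than one visit after baseline: "The time frame will be pre-treatment, post-treatment 10 weeks and after 3 months of follow-up".

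Sample-size calculation says that the future trial will be sized by "sample-size calculations using the effect-size data from this pilot study". Statistical analysis adds that "between-group effect sizes and 95% confidence intervals (CIs) with Hedges correction will be calculated for changes in the secondary outcomes", and that the full-scale size will use the between-subject effect size with at least 80% power, α = 0.05 and a 20% dropout allowance. It mentions no shrinkage, confidence bound or target difference for that step.

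On the pilot's own size: "We will recruit 24 patients for two groups".

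**The concern.** The same 24 patients choose the outcome, filter it by size and supply the effect for the next sample-size calculation. Two selection steps act in the same direction. The larger of two noisy estimates is kept, and then only if its raw difference clears a threshold, which cuts off the low estimates. Hedges correction deals with small-sample bias in one standardised difference. It does nothing about selection.

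The threshold is also demanding for this comparison. A benchmark for change is set against the difference between two arms that both receive 30 sessions of conventional treatment.

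The protocol's stated purpose is to inform a full-scale trial. At stake are that trial's power, the choice of the better outcome, and whether the pilot names any primary outcome at all.

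**Working it through.** **Nothing to reproduce.** The 24 rests on a citation, with no effect size, SD or power behind it.

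**Inputs from the protocol.** 24 patients in two groups, two candidate measures, Hedges-corrected effect, 80% power, α = 0.05, 20% dropout, complete-case analysis, retention goal of at least 80%.

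**Assumptions.** 12 per arm (the ratio is not stated), two-sided α, one visit, correlation of VAS and NDI changes 0.5 (range 0.3 to 0.7), important change 0.3 to 0.8 SD of the change score, true standardised effect d of 0.3 to 0.8.

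**Precision.** SE(d) ≈ √(2/n + d²/(4n)). At n = 12 and d = 0.5 this is √(0.1667 + 0.0052) = 0.41, so the 95% CI half-width is about 0.81. At 10 per arm (80% retention) the SE is 0.45 and the half-width 0.89.

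**Step 1, larger of two.** For equal true effects, E[max] ≈ d + SE·√((1 − ρ)/π) = 0.5 + 0.41 × √(0.5/3.1416) = 0.5 + 0.16 = 0.66. Simulation gives 0.67, and 0.63 to 0.70 for correlations 0.7 to 0.3. One prespecified outcome without the threshold averages 0.50, which is unbiased.

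**Step 2, threshold alone.** Take one prespecified outcome with d = 0.5 and an important change of 0.5 SD. The truncated-normal mean is 0.5 + √(2/12) × φ(0)/0.5 = 0.5 + 0.408 × 0.798 = 0.83, and simulation agrees.

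**Both steps.** Simulated mean g is 0.87 at the same inputs, and 0.91 at 10 per arm. At d = 0.5 it is 0.78, 0.87 and 1.06 for an important change of 0.3, 0.5 and 0.8 SD.

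**Consequence for sizing.** n per arm = 2(1.96 + 0.84)²/d² = 15.68/d², rounded up. The table uses the rule at 12 per arm, correlation 0.5 and an important change of 0.5 SD (200,000 simulated pilots per scenario):

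| True d (both outcomes) | n per arm needed | Median n per arm carried forward | Mean true power |
|---|---|---|---|
| 0.3 | 175 | 29 | 23% |
| 0.5 | 63 | 24 | 44% |
| 0.8 | 25 | 16 | 63% |

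At d = 0.5, power is about 52% with an important change of 0.3 SD and 29% with 0.8 SD. Over the whole grid (d and important change each 0.3 to 0.8), mean g runs from about 0.67 to 1.18, mean power from about 15% to 68%, and the share of pilots in which no outcome qualifies from about 4% to 81%. Approximations in the sizing and power formulas move individual powers by a few points.

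**Picking the weaker outcome.** With true effects 0.6 and 0.4 and no threshold, the difference of the two estimates has SD 0.41 × √(2 × 0.5) = 0.41. P(weaker wins) ≈ Φ(−0.2/0.41) = Φ(−0.49) = 0.31. Simulation gives 32%.

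**No effect on either outcome.** The rule still names a primary outcome in 36%, 18% and 5% of pilots (important change 0.3, 0.5, 0.8 SD), with mean g 0.56, 0.71 and 0.96.

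**The case against.** **The rule is not choosing at random.** A reader might infer that it simply selects noise. The protocol does not support that. Only two measures compete, and the ranking is pure sampling error only if their true standardised effects are equal, in which case neither choice is the weaker one. When they differ, the stronger is picked more often than not: about 68% of the time at 0.6 v 0.4, and 76% at 0.8 v 0.5. This stands.

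**A single power figure cannot be given.** A reader might settle on roughly 40%. That holds only near a true effect of 0.5 and an important change of 0.5 to 0.6 SD. The protocol supplies neither, so the wide range is the honest answer. This stands.

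**Not all of the shortfall belongs to the selection rule.** With one prespecified outcome and no threshold, d = 0.5 and 12 per arm, sizing on the pilot g already gives mean true power of about 68%, and g is zero or negative in 11% of pilots. Part of the loss comes from sizing on a pilot effect at all. This stands, and the fix has to reach that step.

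**The hand-over is inferred.** Statistical analysis computes effects with CIs for every secondary outcome and does not say that only the selected outcome's point estimate feeds the sample size. The inference is reasonable, because a trial is sized on its primary outcome and the text names the effect size as the input, but it remains an inference.

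**The unnamed visit.** The article may leave this to an analysis plan that is not shown, so I do not count it as a fault. The figures assume one visit.

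**The harm is deferred.** The rule changes no patient's treatment and no pilot estimate, and the CIs will be reported, so a later team could set the rule aside. That lowers the severity. It does not make the rule sound.

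**Conclusion.** The point holds as a bias in a stated decision rule. The selected and truncated effect is too large on average in every scenario run. The ranges in the working rest on assumed inputs: 12 per arm, correlation 0.5, equal true effects of 0.3 to 0.8, an important change of 0.3 to 0.8 SD, and the selected g used directly for sizing.

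The threshold is the main driver when the true effect is 0.5 or less and the important change is 0.5 SD or more: at 0.5 and 0.5 it gives 0.83 on its own, and the largest-of-two step brings this to 0.87. At a true effect of 0.8 with the same threshold the inflation is about 1.3-fold (0.8 × 1.3 = 1.04, or 0.24 in total), and the largest-of-two step, worth 0.13 to 0.20, can account for most of it.

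The documents do not support saying that the choice of outcome is mostly noise, that the wrong outcome will usually be chosen, or that the pilot's own reported estimates are spoiled. Severity: should be fixed before the pilot results are used to plan the full-scale trial.

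**What to change.** 1. In Primary outcome measure, delete the largest-effect rule and the between-group threshold. Name the full-scale primary outcome (VAS or NDI) and one visit now, on clinical relevance. Allow a change only on information that does not use the arms: completeness, floor effects, pooled SD and baseline-to-follow-up correlation.
2. In Sample-size calculation and Statistical analysis, base the full-scale size on a prespecified important difference, with the pilot supplying the SD, the correlation and retention. Keep reporting the pilot effects with 95% CIs.

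**Cost.** Text is rewritten in three places and no extra pilot data are needed. The stated full-scale size will probably be larger. If the target difference were 0.5 SD, it would be 2 × 63 = 126, and 126/0.80 = 158 after the dropout allowance. The present rule's median of 24 per arm at a true effect of 0.5 and an important change of 0.5 SD gives 48, and 48/0.80 = 60. For targets of 0.3 and 0.8 SD the totals are 350/0.80 = 438 and 50/0.80 = 63.

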### Sample-size calculation

The sample size of a future, fully powered study will be estimated using sample-size calculations using the effect-size data from this pilot study. We will recruit 24 patients for two groups [37].

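### The future trial's size rests on the effect observed in 24 patients, for the outcome showing the largest effect, so the stated 80% power is missed about half the time from imprecision alone and more often after the selection

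*Protocol article*

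**What the plan says.** Three places in the protocol article act together.

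- Sample-size calculation, listed under Primary outcomes: "The sample size of a future, fully powered study will be estimated using sample-size calculations using the effect-size data from this pilot study".
- Statistical analysis: "between-group effect sizes and 95% confidence intervals (CIs) with Hedges correction will be calculated for changes in the secondary outcomes", and then "Estimated sample size will be determined using the between-subject effect size, with a minimum of 80% power", with α = 0.05 and an allowance for dropout.
- Primary outcome measure, also under Primary outcomes: the full trial's primary outcome will be the patient-reported measure with the largest between-group effect size, on condition that the observed difference exceeds the published minimal important change. The patient-reported measures are the VAS and the NDI.

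On the pilot's own size, the Interventions section says: "Twenty-four patients will be randomized into two groups (study and control) using block randomization". No target difference is given for the future trial, nor any rule for shrinking g or using a confidence limit. The 95% interval is to be calculated, but the size is to be determined from the effect size.

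**The concern.** A size calculated at 80% power has 80% power only if the effect put into the formula is the true one. Here that effect is an estimate from a very small sample, and the formula squares its reciprocal. A g that is too large by chance gives a trial that is too small, and the plan contains nothing to offset this.

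The outcome rule adds a second problem. Taking the larger of two noisy estimates, and keeping it only if it passes a threshold, favours estimates that are too high. The g that reaches the formula is therefore biased upward as well as imprecise.

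A sample-size recommendation is a stated product of this pilot. A later trial that relied on it could be too small to answer its question while being described as fully powered.

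**Working it through.** **Inputs.** From the protocol article: 24 patients in two groups; Hedges g for change scores; at least 80% power; α = 0.05; 20% dropout allowance; complete-case analysis; retention goal of at least 80%. Assumed, because the document gives no value: 12 per arm; two-sided α; true effects of 0.3 to 1.0 SD; VAS–NDI correlation of 0.5 with equal true effects; a minimal important change of 0.3 or 0.5 SD. I also take the effect size entering the formula to be that of the selected outcome, which is the natural reading. The figure of 24 rests on a citation with no effect or SD, so there is no calculation to reproduce.

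**Step 1: precision of g.** Var(g) = J²(2/n + d²/(4n)), with J = 1 − 3/(4·22 − 1) = 0.966 and d = g/J. At g = 0.5, n = 12: d = 0.518, and Var = 0.932 × (0.1667 + 0.0056) = 0.161. So SE = 0.40 and the half-width is 1.96 × 0.40 = 0.79, giving an interval of −0.29 to 1.29. Half-widths at g = 0, 0.5, 0.8 and 1.0 are 0.77, 0.79, 0.81 and 0.82. With 10 completers per arm, about what remains if the retention goal is only just met, they are 0.84 to 0.90.

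**Step 2: one example.** Per arm, n = 2(1.960 + 0.842)²/g² = 15.70/g². An observed g of 0.8 gives 15.70/0.64 = 24.5, so 25 per arm (50/0.8 = 63 in total after dropout). If the true effect is 0.5 SD, the need is 15.70/0.25 = 62.8, so 63 per arm (126/0.8 = 158 in total). With 25 per arm the power is Φ(0.5√12.5 − 1.96) = 42%.

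**Step 3: how often the rule falls short.** I simulated pilots with 12 per arm (60,000 or more per scenario), set n from the observed g and computed power at the true effect. Entries are the share of planned trials with less than 80% power, among pilots that yield a size. They are good to about one percentage point.

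| True effect (SD) | Needed per arm | One outcome, g > 0 | Larger of two | Larger of two, difference > 0.3 SD | Larger of two, difference > 0.5 SD |
|---|---|---|---|---|---|
| 0.3 | 175 | 64% | 74% | 97% | 100% |
| 0.5 | 63 | 54% | 68% | 79% | 94% |
| 0.8 | 25 | 48% | 64% | 67% | 72% |
| 1.0 | 16 | 46% | 63% | 64% | 65% |

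Repeat runs put the lowest one-outcome figure at 43 to 46% and the lowest figure with selection at about 60%. With 10 completers per arm the results are nearly the same or slightly worse. Median power in the last column is 21, 41, 62 and 69%.

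**Step 4: why the threshold hurts.** If the observed difference exceeds the minimal important change, the size computed from it is smaller than the size for the minimal important change with the same SD, apart from the 3% Hedges shrinkage. So the plan tends to give less than 80% power for the very difference it treats as the smallest that matters.

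**Step 5: the alternative.** Fix the target difference and take only the SD from the pilot (22 df). The one-sided upper 80% limit multiplies the SD by √(22/16.31) = 1.16. Then 18 to 20% of planned trials have less than 80% power at the target, and median power is 89 to 90%. With the plain pilot SD the median is 79%, the 10th percentile is 61 to 62%, and about 2% of trials fall below 50%.

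**The case against.** **Imprecision alone does not make a shortfall the usual result.** A reader might infer that the 80% will usually be missed simply because g is imprecise. The figures do not support that. The 54% at a true effect of 0.5 SD applies to pilots with g > 0. Over all pilots it is about 48%, and it is below half at 0.8 and 1.0 SD. The larger shares depend on the outcome rule, and they apply to pilots that pass the threshold.

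**The calculation does not collapse.** A reader might also infer that the rule often yields no size at all, or sizes in the high hundreds. That would ignore the minimal-important-change condition, which removes outcomes with zero, negative or very small effects. With a threshold of 0.3 SD and a true effect of 0.5 SD, the middle 80% of planned sizes runs from about 11 to 98 per arm. This is still wide, but it is finite.

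**The plan is not blind to uncertainty.** It calculates the 95% interval alongside the effect size, and the pilot SD enters through g. Both are true. Neither helps the recommended size, because nothing says how the interval is to influence it.

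**The 20% dropout allowance is not a fault.** It matches the pilot's own retention goal of at least 80%, and 24 patients estimate dropout poorly (4 of 24 has an exact 95% interval of about 5 to 37%).

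**The pilot itself is unaffected.** Its primary purpose is feasibility, judged descriptively against preset goals. This stands, and it limits the severity.

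**Conclusion.** The point holds for the planning rule, and it should be fixed. A minimum of 80% power is not a property of a size computed from g in 24 patients. Imprecision alone leaves about half of the planned trials short (about 43 to 64% for true effects of 1.0 down to 0.3 SD). Choosing the larger effect and requiring it to pass a threshold raises this to about 60% or more, with the share depending strongly on the true effect and the threshold. The ±0.8 SD rests only on the stated sample size and equal allocation. The percentages rest on the assumed true effects, correlation and threshold.

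A reader might infer that 24 patients are too few for this pilot. The documents do not support that: its main aims are feasibility aims, and nothing here affects its conduct or its own analysis. The fault is confined to how the later trial's outcome and size are to be derived.

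**What to change.** Three sections need new wording.

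- **Sample-size calculation and Statistical analysis:** base the future size on a minimal important between-group difference stated in advance for the chosen outcome. Combine it with the SD pooled over arms in the pilot, taken at a conservative value such as its one-sided upper 80% confidence limit (observed SD × 1.16 with 22 df; × 1.18 with 18 df). Other conservative limits would also serve; what matters is to name one beforehand. Keep the 20% dropout allowance.
- **Primary outcome measure:** do not choose the future primary outcome by the largest observed effect. Choose it on grounds that do not depend on the between-group result, such as relevance to patients and completeness of data, which the pilot already records.
- **Statistical analysis:** report g with its 95% interval as description only.

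**Cost.** Patients, visits and data collection do not change. The authors must supply and justify a minimal important difference, for which the article gives no value. The recommended size may be larger. At a target of 0.5 SD, 62.8 × 1.16² gives 85 per arm instead of 63, or 170/0.8 = 213 in total instead of 158 after dropout.
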